### Proposed analyses

Evaluation and analysis of all data collected are ongoing.

#### Quantitative analytic plan

The outcomes analysis will be conducted from the post-training and follow-up assessments of Victim Advocates and Senior Leaders, as well as the continual collection of OMS survey data from caregivers and team members. The variables collected from Victim Advocates and Senior Leaders are the time-varying and CAC-varying *provider fidelity*, *knowledge*, and *perceptions* of the utility of training. In addition, outcomes will include *family engagement*. Statistical analysis will include, but is not limited to, the following: (a) applying linear mixed-effect models to evaluate the changes of the primary outcomes between conditions across time, should the distribution of the outcomes and residuals suggest being appropriate [63, 64]; and (b) investigating the mechanism that is responsible for the causal effect between training conditions and outcomes, with the mediator of knowledge/skill achievement. Covariates collected (e.g., perceived supervisory support, learning anxiety) will also be examined for their influence on the outcome of interest. As a feasibility study, the principal goal at this stage is to conduct an initial examination of training implementation and whether the Victim Advocate knowledge and skills change due to training, what factors might be associated with the change, and how that influences family engagement in mental health services. Further, descriptive statistics will be calculated to examine Victim Advocates ratings of acceptability and satisfaction with the training, as well as rates of attendance in training and consultation.

Missing data will not be avoidable due to the large amount of data collected from sites across the nation, and the repeated measurements across multiple time points. We will examine rates of missing data, as well as data cleanliness, to determine Victim Advocates abilities to complete data submission successfully. Further, stochastic multiple imputation methods will be used to handle missingness, if the assumption of ignorable missing mechanism can be held [65, 66]. In addition, analyses will be “intent-to-treat,” such that individual participants or sites who leave the study will be included in analyses.

All the analysis will be completed by the statistical package R (3.5.2) [67] with multiple packages, such as the dplyr, tidyr, ggplot2, lme4, stats, readr, and mice.

#### Qualitative analytic strategy

The research team plans to conduct thematic analysis of all qualitative responses on evaluation, feasibility outcomes of acceptability and satisfaction, and clinical trial measures. To do so, all responses to each qualitative question will be reviewed in their entirety in order to identify broad themes within the responses. Themes will be organized into a broad codebook, and additional coding will focus on refining themes further. Coding will be conducted by multiple members of the research team, and interrater reliability will be determined through cross-coding of responses and comparison of identified themes. Discrepancies will be reviewed with the larger research team to discuss and finalize coding.

#### Cost analysis

We will generate descriptive statistics from the quantitative cost data to describe typical costs (i.e., means) and variability in costs (i.e., standard deviations) associated with the delivery of the E3 training. Direct costs will be calculated in terms of the cost of the resource and the frequency of its use (e.g., consultation fee x number of consultation sessions). Indirect costs will be calculated by applying a shadow price [68], which estimates the value of lost productivity for alternative professional activities of CAC staff, to time spent on training activities (i.e., hourly shadow price x hours of training activities). All cost estimates will be placed on the same metric through the adjustment to (a) an index year using the Consumer Price Index [69] to account for inflation and (b) national average U.S. dollar values using the Council for Community and Economic Research Cost of Living Index [70] to account for costs of living differences between CAC locations. We will sum all direct and indirect expenses separately before the calculation of descriptive statistics and examine descriptive statistics for total (i.e., direct plus indirect) costs.

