### Consultation plan

The E3w+c training involved two separate orientation training calls for Senior Leaders and Victim Advocates that reviewed the responsibilities and structure of the training. This was followed by 10 web-based consultation calls; Victim Advocates were required to attend 80% for successful completion, and attendance was taken at each call. Calls began weekly in order to solidify learning from the webinars; the final six meetings then took place biweekly. The meetings provided opportunities to individualize learning and practice skills related to mental health screening, engagement (TIES and MI strategies), and linkage to EBP. With Victim Advocates from multiple CACs on each call, there was an opportunity for shared learning, as each participant had the opportunity to share identified barriers encountered and gain feedback from experts and their peers.

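### The cost-of-living adjustment for CAC locations covers all costs, including consultation on web calls shared between CACs, and can add between-site spread that is not real

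*Protocol article*

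**What the plan says.** The Cost analysis section sets out two kinds of cost. A direct cost is a resource price times its frequency of use, and the example given is "consultation fee x number of consultation sessions". An indirect cost is CAC staff time valued as "hourly shadow price x hours of training activities".

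The section then states the price adjustment: "All cost estimates will be placed on the same metric through the adjustment to" an index year, using the Consumer Price Index, and national average dollars, using a cost-of-living index. The reason given for the second step is "to account for costs of living differences between CAC locations". No cost item is excluded, and CACs are the only locations named.

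The results are to "describe typical costs (i.e., means) and variability in costs (i.e., standard deviations) associated with the delivery of the E3 training".

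On delivery, the Consultation plan section says of the orientation sessions: "This was followed by 10 web-based consultation calls". It describes the calls as held "With Victim Advocates from multiple CACs on each call". On attendance, "Victim Advocates were required to attend 80% for successful completion".

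**The concern.** A geographic index suits inputs bought at local prices. CAC staff time is the clear case: wages tend to follow the local cost of living, and dividing by the index makes sites comparable.

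A web call attended at once by advocates from several CACs is a different kind of input. It is one service, and it is hard to see how its price could follow the local price level of every attending site. If its cost is nonetheless divided by each site's index, the same call is recorded as cheaper for a CAC in an expensive area and dearer for one in a low-cost area. Part of the reported variability in consultation cost would then describe where the CACs are, not what consultation costs.

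This has some importance because the Overview of study design makes comparative costs part of the pilot's primary goal and describes consultation as the more expensive element. Future directions says the cost results will inform how training models are compared. The stakes are limited: the cost analysis is descriptive, and no decision rule rests on the standard deviation.

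**Working it through.** The document gives no fee, index value or cost figure, so there is no stated result to reproduce. The check illustrates what the rule does when followed as written.

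**Inputs from the document**
- 10 consultation calls, and 80% attendance required, so 0.80 × 10 = 8 calls for completion (Consultation plan).
- 28 sites in the E3w+c arm (Randomization).
- Direct cost = fee × sessions, then adjusted by the cost-of-living index (Cost analysis).

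**Assumptions, not in the document**
- One uniform fee of $100 per call. With a uniform fee the amount cancels out of every percentage below.
- Local index I, with national average = 1, over three ranges: 0.90-1.10, 0.85-1.25 and 0.85-1.50.

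**Formula:** adjusted cost = fee × sessions / I.

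**Step 1. All 10 calls attended.** Without the geographic step, every site costs 100 × 10 = $1,000, with SD 0. At single index values, 1,000 / 0.85 = $1,176, 1,000 / 1.25 = $800 and 1,000 / 1.50 = $667. With the index spread evenly over 28 sites:

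| Index range | Mean index | Mean cost | SD | SD / mean | Change in mean from $1,000 |
|---|---|---|---|---|---|
| 0.90-1.10 | 1.000 | $1,004 | $61 | 6.1% | +0.4% |
| 0.85-1.25 | 1.050 | $965 | $114 | 11.8% | -3.5% |
| 0.85-1.50 | 1.175 | $876 | $153 | 17.4% | -12% |

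The spread appears in every row. The change in the mean differs in sign and size with the assumed distribution of the index.

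**Step 2. Attendance varies.** Here 8, 9 or 10 calls are drawn with equal chance for each of the 28 sites and I is drawn uniformly over the range, averaged over 4,000 repeats. Without the geographic step the mean is about $900 and the SD about $81, already 9% of the mean.

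| Index range | Mean cost | SD after adjustment | Added SD | SD / mean |
|---|---|---|---|---|
| 0.90-1.10 | $903 | $97 | about $15 | 10.7% |
| 0.85-1.25 | $868 | $124 | about $43 | 14.3% |
| 0.85-1.50 | $786 | $148 | about $66 | 18.8% |

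The added SD is smaller than the $61, $114 and $153 of Step 1, because real variation in attendance already contributes.

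**Step 3. Contrast with local labour.** Take 20 hours at an assumed wage of $25 × I, with I spread evenly over 0.85-1.25. The nominal SD is $61. After division by I every site costs 25 × 20 = $500 and the SD is 0. For this kind of cost the adjustment does what it is meant to do. The difficulty is its scope, not the index itself.

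**The case against.** The strongest reply is that the text does not commit the authors to the harmful reading. The consultation fee appears only as an example of a formula. The document does not say who sets it, who pays it, or that it is equal for all CACs. The purpose stated for the index is to remove differences between CAC locations, and a cost that does not arise at a CAC has no such difference to remove. Indexing the consultants' cost once, where it arises, would give one value for all sites and no false spread. The article is also a condensed account, and a costing plan could assign indices item by item.

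Some of this stands. A reader might infer that the fee is set centrally and is uniform. Shared web calls make a price unrelated to CAC location likely, but the document does not state it, so the point is conditional. A reader might also infer that the mean consultation cost is biased in a known direction. It is not: the sign turns on the unknown index values of the 28 sites. Nor do the documents show that development costs distort per-site figures. The Costs section says these came from the training team to examine overall development cost, and nothing allocates them to sites. Finally, the time advocates spend on calls is local labour, for which the index is appropriate, so only part of the cost of consultation is affected.

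What does not stand is the suggestion that nothing needs changing. The section states a rule covering every cost estimate, names only CAC locations, and gives the consultation fee as a direct cost a few lines before. Indexing by place of origin would cure the problem, but the text does not provide for it. This is a stated rule whose scope is too wide, not merely an omitted detail.

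**Conclusion.** The point holds in a limited, conditional form. As written, the geographic adjustment reaches consultation delivery, which was shared across locations. If the price of a shared call does not vary with the attending CAC's location, the rule adds between-site spread that is not real.

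For a uniform fee with every call attended, the SD goes from 0 to about 6% to 17% of the mean across the assumed index ranges. With attendance of 8 to 10 calls it goes from about $81 to between $97 and $148, on an unadjusted mean of about $900. These figures rest on assumed index values, a uniform fee and, in the second case, equally likely attendance levels.

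The direction and size of any effect on the mean cannot be determined from the document. The same is true of the effect on total E3w+c cost, because the share of consultation delivery in that total is not given. For a descriptive analysis this is a minor correction, but an easy one.

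**What to change.** In the Cost analysis section, limit the cost-of-living adjustment to inputs priced at the CAC's location: CAC wages, shadow-priced staff time and local resources. Leave consultation delivery, and any other cost not incurred at a CAC, in index-year dollars after the Consumer Price Index step, or adjust it once by the location where it arises. State which of the two is used.

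The cost is one sentence in the plan and one marker (local or not local) per cost item in the dataset. No new data are needed. The Proposed analyses section says that analysis is ongoing, so the rule can still be clarified; if cost figures have already been produced, only the consultation items need recalculating and the totals re-summing.

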## Discussion

### Innovation and anticipated contribution

Child maltreatment and co-occurring traumas (e.g., domestic violence, parental substance abuse) are core adverse childhood experiences. Mounting research has demonstrated the immediate and longstanding impact of such experiences on physical and mental well-being [71–73]. Effective mitigation of this negative impact involves timely engagement in EBPs that have demonstrated positive effects on well-being [74, 75]. By providing linkages to services upon the outcry of child maltreatment, service navigators within CACs can facilitate both the immediate connection to needed mental health treatment as well as address “deep-rooted issues related to distrust in providers and the health system that often lead to avoidance of health problems and non-compliance with treatment recommendations” ([76] p. 3543).

The success of previous trials with service navigators within health care settings [76–79] were built upon for the current feasibility study. Uniquely, the service navigator model tested in this project occurs within the CAC, the location of child forensic interviews, and other key interventions provided as part of the investigation of child maltreatment. These multidisciplinary settings are located across the country and connected through the network established by NCA. A nationwide impact on access to EBP for children who experience child maltreatment is feasible given the reach of the 900 CACs across the country [80]. Broadly, no other known existing national system of programs can add one additional component to their existing services (i.e., training Victim Advocates in mental health screening, engagement, and EBP referrals) and have such a widespread impact on the mental health outcomes of children. Given the great potential for change, it was important to pilot training of Victim Advocates to determine whether E3 training could be scaled up, examined in a large-scale trial with child outcomes, and made available to all CACs and Victim Advocates nationwide.

The approach of directly addressing disparities in mental health care is another distinction of this trial. Research has suggested that there are significant socioeconomic disparities in the experience of child maltreatment, such that children living in disadvantaged neighborhoods and poverty are disproportionately affected by abuse and neglect [81]. NCA Accreditation Standards require that CACs provide services to clients regardless of their ability to pay, ensuring that all children receive necessary services. In addition, although previous work has suggested that maltreatment may occur at higher rates in minority populations, this effect is largely due to the poverty and marginalization experienced by certain racial groups [82]. As youth who are not White have been found to be less likely to engage in EBP for a variety of reasons, including experiences of discrimination and racism in the service sector [10, 13, 14], the development and implementation of the E3 training program may help to decrease racial and socioeconomic disparities in the delivery of EBP for children affected by maltreatment. TIES was selected to be a core of E3 training due to its success in enhancing engagement in services by families who are financially disadvantaged and impacted by service disparities [20, 24, 27].

Victim Advocates within CACs are primed for becoming service navigators given their location, role, and responsibilities. Considering the vulnerabilities of and service disparities experienced by the population served by CACs, successful early engagement in mental health services will need to rise above the baseline of providing education, case management, support, and assistance in accessing services. This trial tests the feasibility of integrating well-defined models (i.e., MI and TIES) designed to directly acknowledge and address distrust of service systems and integrate strategies found to reduce internal barriers to change behavior.

Large-scale implementation within complex service systems can be fraught with challenges. The expert recommendation is to construct small changes utilizing the current structure rather than attempt to overhaul the entire system [83]. This logic is readily applied to the current project, as the Victim Advocate position is already embedded and integral to the work of CACs. The E3 training is designed to enhance their capacity, testing whether enhanced skills of the Victim Advocate and the success of early engagement in EBP can be readily accomplished with web-based training alone (E3w) or significantly augmented through consultation (E3w+c). The results of this feasibility study will inform a larger randomized trial, integrating longitudinal design to examine the impact of Victim Advocate training on the child and family outcomes, as well as potential cost/benefit implications. If successful, the E3 project can inform the development of family navigator models for other settings (e.g., schools) [84] and clinical problems (e.g., problematic sexual behavior, for which service responses are even more challenging to coordinate than for maltreatment) [85]. Determinations of success will include the impact of the training on clinical trial outcomes, such that we see changes and improvements in mental health screening, use of engagement skills, and attendance at mental health sessions. Further, feasibility success will be determined by obtaining high rates of satisfaction and acceptability on training evaluations (ratings of 4 or 5 on Likert scale), high rates of attendance and completion of webinars and consultation (80% completion), and successful data submission.

### Limitations/practical and operational challenges

Although the current project offers many strengths, limitations and potential challenges warrant comment. Initial plans for data collection were to utilize NCATrak, NCA’s proprietary tracking software used by CACs to record data on their clients served, anticipating that most sites would be using the software. However, upon the investigation of the potential CAC sites’ procedures, the variety of database programs used, and the number of changes required for each system, the use of NCATrak was determined to be impractical for the collection and integration of data across CACs for the current project. As such, we shifted data collection to one central system, REDCap. However, the decision to use REDCap has not been without challenges, as we have had to train Victim Advocates on the system’s procedures and activities. Creating training videos on REDCap procedures and holding open “office hours” with the research team for troubleshooting concerns have facilitated the process. Future trials of the E3 training may benefit from additional data submission support for CACs, such as research technicians who can collect and enter data directly, in order to decrease the burden on Victim Advocates.

Further, to examine fidelity to the model, Victim Advocate implementation of engagement strategies like MI and TIES had to be collected via self-report methods, as observational methodologies were not within the scope of the feasibility project budget. Research has suggested that professionals are able to reliably self-report on their use of intervention techniques with a high level of concordance with an observer and expert ratings of the same variables [86, 87]. However, observational methodologies are planned to expand the examination and verify changes in skills in the next step of the research and larger-scale project.

A third limitation of the study is our ability to address all of the unique barriers faced by each family and CAC. The E3 training encouraged Victim Advocates to assess and address all of the potential barriers faced by their families, using evidence-based motivational strategies to improve their engagement in EBP. However, it is possible that the training’s focus on knowledge and skills of MI and TIES subsequently caused other important barriers to be missed. Future research may benefit from individualized assessment of the barriers within communities and additional training to Victim Advocates on best methods to tailor their responses to each family.

An unfortunate challenge that was unable to be addressed within the current study is the fact that mental health services, particularly EBP, are not readily available across all communities. The E3 project required that sites have linkage agreements with or provide on-site mental health services providing EBP, and Victim Advocates were trained to recognize EBP. However, it is possible that families were still unable to access quality services in their communities for myriad reasons. It is possible that only non-EBP were available in certain communities or for specific problem types. Alternatively, long waitlists may make access to services challenging, particularly for providers of color, who are significantly underrepresented in the mental health field. For BIPOC youth and families, being able to access services with a provider of color may have been important yet even more difficult to find. The challenges of EBP saturation and availability were beyond the scope of the E3 project but will have an impact on outcomes. As such, future research should consider direct measurement of these variables, as they are important potential mediators of outcomes.

The rate of job turnover of CAC personnel was also an unanticipated challenge in the current project. In response, we added measures related to turnover intent, job satisfaction, and burnout to the post and follow-up data collection waves to understand better this phenomenon within the CAC. Our experience highlights the importance of using a readily accessible, effective training platform, and the need to examine the impact of training on job retention. Previous research has demonstrated that training in EBP with associated consultation significantly improved job retention of bachelor’s level home-based parenting service providers working with vulnerable families (i.e., half the job turnover rate than the other conditions) [88]. Currently, we are implementing an intent-to-train analytic plan by asking those sites who left the training to complete data collection at post-training and follow-up. Lessons learned from this feasibility trial will inform a large randomized trial in the future.

Finally, another unanticipated difficulty has been COVID-19. The pandemic and related stay-at-home orders had a direct and profound impact on CAC activities as well as on the well-being of CAC staff and the families they serve. Transitioning CAC services to tele-health platforms was essential. Throughout the crisis, we endeavored to provide support to Victim Advocates in their understanding and skill in administering the screener and using TIES and MI strategies via the phone and telehealth platforms. By providing video training and additional consultation, we hoped to broaden the CACs’ use of the training. In addition, flexibility and changes in the timeline allowed CACs space to adjust to the changes caused by COVID-19 and improve learning. Finally, measures of COVID-19 impact on well-being and CAC functioning were integrated into post- and follow-up data collection waves, which will provide opportunities to examine the process of family engagement during considerable stress and strain.

